# Health Information and Monitoring of Sexually Transmitted Infections (SIM study): a single-center, parallel, three-arm randomized controlled trial protocol for enhancing adherence to syphilis treatment and follow-up

**DOI:** 10.1186/s13063-022-06383-w

**Published:** 2022-05-26

**Keywords:** Syphilis, Clinical trial, Telemonitoring, Treatment adherence, Protocol, Randomized controlled trial

## Abstract

**Background:**

Syphilis has recently resurfaced as a significant public health problem. Since the 2000s, isolated syphilis outbreaks have increasingly occurred in North America, Europe, and Australia; in Brazil, there have been progressive increases in both congenital and acquired syphilis. There are several possible explanations, such as misdiagnosis of acquired syphilis, which could increase the number of untreated transmitters in the population; failure to initiate or complete treatment; and nontreatment of sexual partners (leading to reinfection). Mobile technologies have been successfully used to promote behavior changes and can positively impact treatment and follow-up adherence in patients with infectious diseases. The purpose of this clinical trial is to evaluate treatment and monitoring methods in patients with syphilis, including follow-up by telephone, via a game in a smartphone app, and at public health centers.

**Methods:**

The SIM study is a single-center, randomized controlled trial with a 12-month follow-up period. The aim is to identify the most effective method of follow-up regarding patient compliance with treatment. The tests will be performed in a mobile unit in easily accessible locations. The goal is to perform 10,000 rapid tests for syphilis. Patients with a confirmed diagnosis according to VDRL tests will be randomized to one of three arms: telephone, smartphone game, or conventional in-person follow-up. All analyses will follow the intention-to-treat principle.

**Conclusion:**

If we find differences in effectiveness, a major change in the conventional approach for this patient population may be needed, potentially affecting current Brazilian health policy strategies.

**Trial registration:**

NTC04753125. Version 1 of protocol 1/09/2020.

**Supplementary Information:**

The online version contains supplementary material available at 10.1186/s13063-022-06383-w.

## Introduction

Syphilis infection has recently re-emerged as a significant public health problem, with an increasing incidence in many countries [1]. Syphilis is a bacterial infection caused by *Treponema pallidum*; transmission occurs through sexual contact (acquired syphilis) or during pregnancy (vertical transmission) [2]. The primary lesion (primary syphilis) frequently goes unnoticed, and many individuals do not notice any symptoms during the early stages of infection. Congenital syphilis, on the other hand, occurs when a mother infected with syphilis transmits the infection to her child during pregnancy; in these cases, the disease has a poor prognosis, and the risks of spontaneous abortion, fetal death, and premature infant death are increased [3].

Beginning in the 2000s, a growing number of isolated syphilis outbreaks were reported in North America, Europe, and Australia, primarily within sexual networks of men who have sex with men (MSM); syphilis infection is often associated with HIV coinfection and cotransmission [4]. While the number of cases in specific groups has increased in high-income countries, in low-middle-income countries, syphilis remains an endemic disease, affecting the general population [5].

In Brazil, there has been a progressive increase in both congenital and acquired syphilis in recent years. Data from compulsory reports indicated that acquired syphilis rates increased from 2.0 cases/100,000 inhabitants in 2010 to 58.1 cases/100,000 inhabitants in 2017. Congenital syphilis also increased substantially (3.6-fold) from 2.4 to 8.6 cases per 1000 live births. Although these increases occurred in all Brazilian regions, some geographical regions had rates above the Brazilian average, including the Southern Region, in which the city of Porto Alegre had an incidence rate of congenital syphilis 3.8 times higher than the rate in the Brazilian general population [6, 7].

Several causes could be implicated in the increasing number of cases, such as misdiagnosis of acquired syphilis, which could lead to a larger number of untreated transmitters in the population; failure to initiate or complete treatment; nontreatment of sexual partners (leading to reinfection); or lack of adequate prenatal care, as syphilis is most often diagnosed during pregnancy screening or during screening for other sexually transmitted infections [7].

There are 8.3 billion mobile phone subscriptions worldwide; this number is greater than the global population, and the numbers of subscribers in low- and middle-income countries are increasing rapidly, thereby increasing opportunities to easily connect with a large number of patients to provide individual-level support [8]. Telemedicine by phone has increased widely in the country and in different areas. Although telemedicine has been shown to promote follow-up adherence to treatment protocols for chronic conditions [9–11], there is no evidence of its impact on STIs. Additionally, there is pressure in the country for its implementation. Regularly followed patients were chosen as the control group.

Herein, we describe the study protocol for a parallel randomized controlled trial to evaluate different home telemonitoring technologies to enhance adherence to treatment and follow-up in syphilis patients.

Mobile technologies and strategies to track test results and appointments have been successfully used as tools to promote behavior changes and can positively impact adherence to treatment and follow-up in patients with chronic [9, 12–14] and infectious diseases [10, 11, 15, 16]. The main hypothesis is that participants who are allocated to the game will have greater adherence to syphilis treatment and monitoring than contacts with telephone contact, and both intervention arms will have better adherence to treatment and follow-up than those randomized to conventional attention. The app group will be compared to the telephone calls and conventional attention groups, and the telephone call arm will be compared to the conventional attention.

## Materials and methods

### Study design

The SIM study is a single-center, superior, randomized controlled trial with a 1:1:1 allocation ratio that includes three parallel arms: (1) follow-up with telephone calls, (2) follow-up using gamification in a mobile app, and (3) follow-up with usual care provided by the public health system. The conventional strategy in Brazil involves through mandatory notification by the physician and guidance to the patient, but it does not consist of an active search through home visits or telephone contacts. Randomization will occur at the individual level.

### Participants and recruitment

All adults aged 18 years and older will be invited to answer a questionnaire to collect socioeconomic and sexual behavior data and undergo rapid tests for syphilis, HIV, and hepatitis B and C in a mobile unit located in an area accessible to a large population. The unit will have different attractive features, such as free internet, charging areas for smartphones, and shaded and rest areas with screens, to increase the participation rate. All participants will receive an ecobag plus preservatives and lubricants. Participants with a positive rapid test will be invited to undergo confirmatory testing. This protocol was written following the Standard Protocol Items: Recommendations for Interventional Trials (SPIRIT) statement to define the clinical trial protocol.

### Eligibility criteria

The study will be carried out in Porto Alegre, Southern Brazil. Participants who do not return after three contact attempts will be excluded from the study, as will pregnant women, participants who are not able to provide contact information, participants who are illiterate and those who underwent syphilis treatment within the previous 3 months.

### Sample size

Considering a confidence level of 95%, an incidence rate of 93.7 per 100,000 inhabitants in the municipality of Porto Alegre [9], and an acceptable difference of 60.0 per 100,000 inhabitants, it is estimated that testing 10,000 individuals will be necessary to obtain an accurate prevalence of syphilis in the municipality. This sample will serve as the basis for the inclusion of patients in the clinical trial.

For the randomized clinical trial, another sample size calculation will be considered. Using a previous article in which 16.5% of the participants who were diagnosed with syphilis received appropriate treatment and 55.9% received inappropriate treatment as a reference, it is expected that at least half of the latter group will eventually receive proper treatment, for a total of 44.45% receiving appropriate treatment [17]. Thus, considering a sample size calculation to detect differences in the proportions of adequate treatments between groups, using a 95% confidence level, 80% power, and a maximum loss rate of 20%, 51 participants in each study group will be needed.

The primary goal of the study is to compare treatment adherence and follow-up among the three parallel study arms. The groups will be compared as a whole, and if relevant, pairwise analysis will be conducted. Such comparisons will be performed using the chi-square test and adjusted residuals when necessary. We will investigate the association between treatment

adherence and sociodemographic, sexual health, and sexual behavior variables as secondary outcomes. The association will be estimated by calculating crude and adjusted odds ratios (ORs) using logistic regression, also addressing confounding variables. Intention-to-treat analysis will be used to assess the clinical effectiveness of the intervention.

We anticipate a minimal number of missing values given that the study variables will be collected by trained researchers. However, data quality analysis will be applied to identify inconsistencies and missing data, and meetings with the researchers will be conducted to discuss missing data and prevent further inconsistencies.

A statistical significance level of 0.05 will be adopted for all statistical analyses. R software, version 4.0.3, will be used for the analysis.

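### The 10,000-test target enters an incidence rate as a prevalence, and its stated ±60 per 100,000 cannot hold if the same people supply the 153 trial patients

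*Protocol article*

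**What the plan says.** The Sample size section of the protocol article contains two calculations.

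The first sizes the testing campaign. Its inputs are a 95% confidence level ("Considering a confidence level of 95"%), "an incidence rate of 93.7 per 100,000 inhabitants in the municipality of Porto Alegre" and "an acceptable difference of 60.0 per 100,000 inhabitants". Its conclusion is that "it is estimated that testing 10,000 individuals will be necessary to obtain an accurate prevalence of syphilis in the municipality". The section then ties the campaign to the trial: "This sample will serve as the basis for the inclusion of patients in the clinical trial".

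The second sizes the trial by comparing proportions adequately treated. With "a maximum loss rate of 20%, 51 participants in each study group will be needed". The Study design section describes a "randomized controlled trial with a 1:1:1 allocation ratio that includes three parallel arms", so the total is 153. The Methods part of the abstract repeats the goal of 10,000 rapid tests and limits randomisation to patients whose diagnosis is confirmed by VDRL.

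**The concern.** The first calculation names its input an incidence rate and its target a prevalence. These are different quantities. Incidence counts new cases over a period, while a one-off test of attendees finds whatever infection is present, however long it has been there. The article's Introduction itself says that early infection often goes unnoticed and lists misdiagnosis among the possible reasons for untreated transmitters, so new cases per inhabitant are a weak guide to what screening will find.

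The paragraph also gives the 10,000 people two jobs: to estimate prevalence within ±60 per 100,000, and to supply the trial. The first holds only if syphilis is rare among those tested, and the second only if it is far more common. At stake are the stated precision of the prevalence estimate, the population it is said to describe, and whether a reader can see what yield the recruitment plan relies on.

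**Working it through.** **Inputs** (protocol article, Sample size, unless noted)
- Rate used as the expected proportion: p = 93.7/100,000 = 0.000937
- Margin: d = 60/100,000 = 0.0006
- Confidence: 95%, taken as two-sided, z = 1.96 (the article does not state sidedness)
- Tests: 10,000
- Trial size: 51 per arm; three arms at 1:1:1 (Study design), so 3 × 51 = 153

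**Step 1: reproduce the 10,000.** For a single proportion, n = z² p(1 − p)/d².

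1.96² × 0.000937 × 0.999063 / 0.0006² = 9,989

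This matches the stated 10,000. At exactly 10,000 tests the half-width is 1.96 × √(0.000937 × 0.999063/10,000) = 0.00060, or 59.97 per 100,000. Other readings do not reproduce the figure: a one-sided z gives 7,035; 60 as the full interval width gives 39,956; a one-sample test with 80% power gives 15,798 or 23,993, depending on direction; and a two-sample comparison with 80% power gives 27,758 or 53,872. So the incidence rate was entered as the expected prevalence.

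**Step 2: cases implied by the stated input.** 10,000 × 0.000937 = 9.4, against 153 needed. At that rate, 153 cases would take 153/0.000937 ≈ 163,300 tests.

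**Step 3: prevalence implied by the stated recruitment.** 153/10,000 = 1.53%, which is 1.53/0.0937 = 16.3 times the planning value. It is a floor, reached only if every confirmed case is eligible, consents and is randomised. The exclusions under Eligibility criteria (failure to return, pregnancy, no contact information, illiteracy, recent treatment) push the required prevalence above it.

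**Step 4: precision at that prevalence.** 1.96 × √(0.0153 × 0.9847/10,000) = 0.00241, or ±241 per 100,000. That is 240.6/60 = 4.01 times the stated margin. Keeping ±60 at 1.53% would take about 160,800 tests.

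**Step 5: can both statements hold?** A half-width of at most 60 per 100,000 from 10,000 tests requires p(1 − p) ≤ 10,000 × (0.0006/1.96)² = 0.000937. For a rare condition that means p of at most about 93.8 per 100,000. Recruitment requires at least 1,530 per 100,000. The two ranges do not meet.

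**Step 6: relative precision, and higher prevalences.** The article gives no prevalence, so the last three rows are assumptions for illustration.

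| Prevalence among those tested | 95% half-width per 100,000 | Multiple of 60 | Half-width ÷ prevalence |
|---|---|---|---|
| 0.0937% (planning input) | 60 | 1.0 | 64% |
| 1.53% (floor for 153) | 241 | 4.0 | 16% |
| 2% (assumed) | 274 | 4.6 | 14% |
| 3% (assumed) | 334 | 5.6 | 11% |
| 5% (assumed) | 427 | 7.1 | 8.5% |

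As prevalence rises over this range, absolute precision worsens and relative precision improves.

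**The case against.** The strongest reply is that the article never offers 93.7 per 100,000 as the expected yield of the mobile unit. It says only that the tested sample is the source of trial patients. A reader might infer from the 9 cases that the plan predicts its own recruitment failure. The documents do not support that: the figure follows from using the rate as a prevalence, which is the very step in question, and the Introduction's remarks on unnoticed infection suggest that screening could find much more. This part of the reply stands.

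A second reply is that 10,000 tests may serve the prevalence aim well. If the trial recruits, the relative margin falls from 64% to about 16% or less. This also stands, so the number of tests need not change. What fails is the stated ±60.

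A third is that the error leaves the trial alone. The 51 per arm comes from a separate calculation (16.5% against 44.45%) that does not use the incidence rate, and prevalence is not among the endpoints under Outcome assessment. A reader might infer that the trial's power is compromised; nothing in this paragraph supports that.

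A fourth is that the Monitoring and quality control section plans a one-month pilot and a 6-month interim analysis that may recalculate sample size or change eligibility. These allow a response to slow recruitment, but they do not correct the stated input or precision.

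Finally, a full breakdown from positive test to consent may sit in the complete protocol, and its absence from an article is no fault. The point made here is different: figures that are stated conflict within one paragraph.

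**Conclusion.** The point holds as a wrong input and an internal inconsistency. It is not an arithmetic error: 9,989 follows correctly from the numbers entered. The stated rate and the stated ±60 per 100,000 cannot stand beside recruitment of 153 patients from the same 10,000 people. Either the sample contains about 9 cases, or the margin is at least ±241 per 100,000, four times what is stated.

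This rests on a two-sided 95% normal-approximation interval, on all 153 patients coming from the 10,000 tested, and on 51 in each of three arms. Fourfold is the minimum; any loss between confirmation and randomisation widens the gap.

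A related fault is the target population. The Participants and recruitment section describes people who choose to attend a mobile unit equipped with attractions, and no sampling of residents is described. The article therefore supports an estimate for attendees, not for the municipality.

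The point deserves correction but is of moderate weight. The randomised comparison, its sample size and its stated power are untouched.

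**What to change.** Rewrite the first paragraph of the Sample size section, keeping 10,000 tests and 51 per arm:

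1. Replace the incidence rate with an assumed prevalence of confirmed syphilis among people tested at the mobile unit, and give its basis.
2. Restate the 95% half-width that 10,000 tests give at that prevalence, in absolute and relative terms. At 1.53%, for example, it is ±241 per 100,000, or about 16% of the estimate.
3. State that at least 1.53% of those tested must end up randomised to reach 153. This also gives the 6-month interim review a figure against which to judge recruitment.
4. Describe the result as prevalence among mobile-unit attendees, not in the municipality.

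The cost is one paragraph of text, a wider stated absolute margin and a narrower prevalence claim. Neither the number of tests nor the trial design changes.

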### Study procedures

A paper-based questionnaire to collect sociodemographic, behavioral, and health information will be administered to all participants to check eligibility, and a rapid test for syphilis will be performed. All participants with a positive test result will undergo confirmatory testing. Upon the receipt of confirmatory test results, the participants will be invited to take part in the clinical trial, and a web-based questionnaire will be used to collect information such as age, sex, social class, education level, alcohol consumption, tobacco and drug use, risk for syphilis, history of hepatitis and other sexually transmitted infections (STIs), number of sexual partners, type of sex and condom use. The main objective of the trial is to test strategies to improve adherence to follow-up. Overall, to increase awareness regarding syphilis, all participants will receive informative folders on syphilis, HIV, and hepatitis prior to randomization. Adherence will be monitored by the number of accesses to the application and by successful telephone calls.

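### The 10,000 tests are justified as giving an accurate municipal prevalence, but as described they estimate the proportion positive among volunteers at a mobile unit

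*Protocol article*

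**What the plan says.** The Sample size section of the protocol article has two calculations. The first sizes the screening. It uses 95% confidence, "an incidence rate of 93.7 per 100,000 inhabitants in the municipality of Porto Alegre" and "an acceptable difference of 60.0 per 100,000 inhabitants", and concludes that "testing 10,000 individuals will be necessary to obtain an accurate prevalence of syphilis in the municipality". The same tests are then to supply patients for the trial, which is sized separately at 51 per arm.

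On where the tested people come from, Participants and recruitment says that all adults aged 18 or over will be invited to answer a questionnaire and be tested "in a mobile unit located in an area accessible to a large population". It adds: "The unit will have different attractive features, such as free internet, charging areas for smartphones", with the aim of raising participation. The Methods part of the Abstract likewise places the testing at easily reached sites.

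Eligibility criteria names Porto Alegre as the place where the study is carried out and lists exclusions. None of them concerns residence. No sampling frame, random selection of sites or people, or weighting is described.

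**The concern.** A precision calculation for a proportion gives the width of the interval around an estimate for the population that was sampled. It carries over to the municipality only if those tested are a random sample of its inhabitants, or if the analysis corrects for how they were selected. People who stop at a mobile unit and accept free testing for sexually transmitted infections may differ in risk from residents in general, and some may not live in the city. The size and direction of the resulting bias are unknown, and testing more people does not reduce it.

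What is at stake is the label on the result. Under Dissemination, reports go to the Ministry of Health and to government agencies. A figure presented there as the prevalence in Porto Alegre, with a tight interval, would look more certain than the design allows.

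**Working it through.** **Inputs, all from Sample size.** Planning rate p = 93.7/100,000 = 0.000937. Tolerance d = 60/100,000 = 0.0006, read as an absolute half-width. Confidence 95%, taken as two-sided, z = 1.96.

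**Step 1: reproduce the 10,000.**
n = z² p(1 − p)/d² = 1.96² × 0.000937 × 0.999063 / 0.0006² = 9,989.5, so 9,990. This matches the stated 10,000. A one-sided reading gives 7,036 and does not match. The arithmetic is sound. The formula has no term for a design effect or for selection.

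**Step 2: what the margin means in counts.**
At n = 10,000 the half-width is 1.96 × √(0.000937 × 0.999063 / 10,000) = 59.97 per 100,000. Expected positives are 10,000 × 0.000937 = 9.37, and the tolerance is 10,000 × 0.0006 = 6 positives.

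**Step 3: how much selection uses up the margin.**
Let r be the ratio of prevalence among attendees to prevalence in the municipality. The bias is (r − 1) × 93.7 per 100,000. It equals ±60 when r = 1 + 60/93.7 = 1.64 or r = 1 − 60/93.7 = 0.36. The documents give no value for r, so these are illustrative thresholds.

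**Step 4: effect on the interval.**
Assume a true municipal value of 93.7 per 100,000, n = 10,000 and an exact 95% binomial interval. The chance that the interval contains the municipal value is:

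| Assumed r | Bias per 100,000 | Coverage |
|---|---|---|
| 0.5 | −46.85 | 68.8% |
| 1 | 0 | 96.8% |
| 1.25 | +23.4 | 91.1% |
| 1.5 | +46.85 | 75.1% |
| 2 | +93.7 | 31.2% |
| 3 | +187.4 | 1.0% |

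**Step 5: does more testing help?**
Four times as many tests would halve the half-width to about 59.97/2 = 30 per 100,000 and leave the bias column unchanged. No replacement sample size follows from this point.

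**Step 6: dependence on the planning rate.**
The threshold of 1.64 belongs to the planning rate. The trial needs 3 × 51 = 153 patients from the same 10,000 tests, a yield of at least 1.53%. If prevalence were at that level (an assumption), the half-width at n = 10,000 would be about 241 per 100,000, and the ratio that uses it up would be 1 + 241/1,530 = 1.16. The conclusion therefore does not depend on the low planning rate. Using an incidence rate to size a prevalence estimate is a separate matter.

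**The case against.** Four things can be said for the plan.

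First, prevalence is not among the outcomes listed under Outcome assessment, nor among the aims in the Abstract. It appears in one statement that justifies the screening volume, and the trial has its own calculation. This stands, and it limits the weight of the point.

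Second, an article condenses its protocol. Site rotation, weighting or a residence item may sit in the full document, and the sociodemographic questionnaire is not listed item by item. This stands in part. It rules out saying that residence is not recorded, or that no municipal estimate could ever be made. It does not answer the mismatch between two things the article does state: a municipal target sized by a random-sample formula, and recruitment by open invitation.

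Third, the bias may be small. It may, but nothing in the document bounds it.

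Fourth, a reader might infer that the trial's exclusions are applied before testing. Study procedures says that a questionnaire "will be administered to all participants to check eligibility, and a rapid test for syphilis will be performed", and the exclusions include "those who underwent syphilis treatment within the previous 3 months". On that reading, pregnant, illiterate and recently treated people would be missing from the prevalence sample, and leaving out the recently treated would pull the estimate down. The document does not support this. Participants and recruitment invites all adults to be tested. Study procedures puts the trial invitation after the confirmatory result. The exclusion for not returning after three contact attempts makes sense only after testing. The wording is ambiguous enough to need a clarifying sentence, and no more.

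**Conclusion.** The point holds, as a minor one. The 10,000 is computed correctly, but the property claimed for it, an accurate prevalence for the municipality, does not follow from the recruitment described. As written, the result is the proportion positive among adults attending the mobile unit, and the 60 per 100,000 is a margin for sampling error around that quantity.

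The size of any bias cannot be determined from the document. The ratios and coverages shown are illustrations that assume the planning rate is the true municipal rate.

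Two stronger conclusions should not be drawn: that the design makes a municipal estimate impossible whatever the full protocol contains, and that the trial itself is compromised. Randomisation takes place among confirmed patients, so how attendees were drawn to the unit does not bias the comparison of the three arms.

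**What to change.** 1. In Sample size, replace the municipal target with the proportion positive among adults attending the mobile unit, and state that the margin reflects sampling error only.
2. Add a sentence to Study procedures that every tested adult is counted in this proportion, whether or not eligible for the trial. This may already be the intention.
3. Base any statement about Porto Alegre on attendees recorded as residents, and label it volunteer-based. Record municipality of residence if the questionnaire does not already do so. Standardising by age and sex would not remove self-selection on risk and, with about 9 positives expected at the planning rate, would be unstable. It is no substitute for the label.

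The cost is a few sentences, possibly one questionnaire item, and a more modest prevalence claim. Nothing in the randomisation, the trial's outcomes or its analysis changes.
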